### Data collection

Written Informed consent is sought from all participants. A thumb impression and signature of a witness is taken for illiterate participants [40]. Data is collected by trained researchers in two stages using a paper-pencil method. In the first stage, demographic data along with GHQ-12 is collected. The data collectors score the GHQ-12 using a scoring sheet and if the participant has a score of 3 or more, secondary outcome data is collected at the same time. The questionnaire for secondary outcome data takes 40–45 min to complete. Participants are not compensated for their time, as this is a volunteer-led intervention. Data collection staff travel to participant’s home for data collection to avoid any travel costs for participants. Data collectors are recruited from the intervention district but recruited from different villages. Data collectors are not paired (based on age, gender, caste, and religion) with participants and they are not assigned participants from their villages for data collection, thus reducing the likelihood of study staff having prior acquaintance with the participants. Furthermore, if any study staff had any prior personal acquaintance with a participant, they were replaced with another data collector who was not acquainted with the participant.

### Data management

*Atmiyata* uses a comprehensive data management system that aids in collecting high-quality data by maintaining on-going- on-site and off-site quality assurance and quality control checks. Research staff (data collectors) handling data are thoroughly trained in interview techniques and procedures for sensitive data handling. Several measures to control for quality of data collected are implemented, including weekly checks, field monitoring visits twice a month by data manager and spot checks (once a month). Additionally, refresher training sessions are provided once in 4 months for quality assurance purposes. The data manager ensures completeness and legibility of the data prior to data entry and is responsible for storing all the data. A designated data entry person is trained for specific entry guidelines to avoid erroneous data entry. The de-identified data is entered in a password-protected Excel sheet. Personally identifiable information is not entered in the database. Raw data is not uploaded on the internet; instead all entered data is shared with the statistician through offline electronic data transfer from the site by the project manager on a monthly basis. The statistician collates the data, maintains the database, and reviews data quality in terms of numbers, consistency and completeness. Measurement of percentage agreement among the data collectors is obtained once a year, to ensure the reliability of the data collected. Several strategies are adopted to achieve adequate participant enrolment including three telephonic follow-up calls to participants not available during in-person visits, two reminders for follow-up visits and rescheduling visits as per participant convenience. Recruitment, follow-up rates, and missing data are discussed at monthly team review meetings between a data manager and data collectors.

### Data storage, security, and confidentiality

Study data is anonymized using unique study identification codes for participants, which is matched to the physical consent form and then entered in the study database. Only the consent form includes personally identifiable details. A code sheet linking the participant’s personal identifiable information is linked to the unique study identification code. Data is stored on a password-protected external hard drive periodically as a back-up. All consent forms and data forms are stored in a locked cabinet at the site office in Mehsana, accessible only to the PI and data manager. After the study is over, the data will be stored in the sealed cabinet as required by Indian regulations.

### Data monitoring

An advisory committee consisting of 4 experts in medical ethics, public health administration and public health and social science research was formed to monitor the implementation and research. The Committee meets every 6 months with the research team and makes periodic site visits to personally interact with a few participants. All adverse events will be reported to the committee.

### Statistical analysis

Baseline characteristics will be summarized using counts (percentages) for categorical variables and means (SD) for continuous variables. The analysis will be based on intention to treat and participants will be analyzed in the group that the cluster was assigned to at each time point.

The analysis plan is based on the Hussey and Hughes model for the analysis of cross-sectional SW-CRCT designs [15]. Generalized Linear Mixed Model (GLMM) will be used to determine the size and direction of the difference between the control and intervention conditions for primary and secondary outcomes. The estimated intervention effect will be reported as the mean outcome difference for continuous variables and Odds Ratio for categorical variables between intervention and control condition assuming a constant treatment effect over time. Estimates of the difference and 95% CIs will be calculated. To take the time effect into account, all analyses will be adjusted for time (periods) of the intervention and clusters. Period (time) and intervention (counseling sessions) will be specified as fixed effects and clusters as a random effect. The analysis will be adjusted for baseline covariates to account for potential imbalance arising due to different recruitment procedures and regional differences across control and intervention conditions. The analysis plan does not include any interim analyses.

Two broad model extensions [41], random cluster by period effect and random cluster by treatment effect will be used for secondary analysis. The secondary analysis will investigate an interaction effect between intervention and time and the interaction effect between cluster and time. Additional analyses of the primary outcome will be conducted controlling for demographic variables if required. Statistical analyses will be carried out using STATA version 14 [38].

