### Recruitment

In the control condition (enhanced usual care), a screening list is generated from the district electoral roll using a systematic random sampling method with pre-decided random start and random interval, with every *n*th number from the pool being selected. We used electoral roll as it is the most complete, comprehensive and accessible national frame of residential addresses in India and electoral rolls are extensively used for drawing a random sample from the general population [39]. For each group of clusters (A, B, C, and D) electoral rolls from all the villages under 14 PHCs are included. Since the prevalence of CMD is 4–8%, according to the National Mental Health Survey, India [1], a screening list using a minimum prevalence of 4% and assuming 25% missing persons is prepared. For each group (A, B, C and D) in each period of the control condition, a screening list of 1800 participants is created and screened (GHQ-12 score of 3 and above) to achieve the target sample of 56 participants.

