A different recruitment procedure is used in the intervention condition, as using structured questionnaires for identification (e.g. GHQ, PHQ) was perceived as impractical when implementing the intervention at scale and seen as stigmatizing in a community setting. Champions are trained to identify a person in their catchment area (i.e. villages) with CMD based on symptoms described by the participant during an unstructured interview. When a Champion identifies a person with CMD to whom they intend to provide 4–6 counseling sessions to, they are asked to inform their CF who in turn informs the data manager who creates a caseload list for each Champion. All caseload lists across Champions are then merged to create a master list. The master caseload list has the residential address of the persons identified by the Champion, who are then approached by the data collection team. Champions obtained verbal consent from each person before providing any personal information such as the address to the CF. CFs are trained to maintain confidentiality of this information (see the section on data storage, confidentiality below). The sample for the intervention condition is drawn from this master caseload list using a computer-generated random method. The drawn sample is screened by data collection staff using GHQ-12 (score of 3 and above) for recruiting intervention participants. This screening and subsequent baseline data collection for participants meeting the inclusion criteria is done prior to the Champion starting psychosocial counseling sessions with the participant. This process is continued until the target sample size of 56 cases is reached for each cluster and period. A different recruitment procedure for the intervention condition was chosen in order to estimate the specificity (accuracy) of ident ification of CMD cases by Champions, which is one of the secondary outcomes. Using similar recruitment procedures in both control and intervention condition (using electoral rolls) would have answered the coverage question (how many people with CMD in the community were identified by the Champion) but not allow us to assess accuracy of identification. We first want to establish whether Champions are accurately able to identify persons with CMD, before addressing the coverage question. Furthermore, we have other data to estimate the population coverage of the intervention.

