## Discussion

*Atmiyata* is a community-led intervention focused on reducing distress, particularly depression and anxiety symptoms in rural communities in India. The evaluation of the intervention through SW-CRCT, offers several unique opportunities. There is limited literature on SW-CRCTs conducted in low and middle-income countries, particularly involving mental health interventions. This study will contribute to this sparse evidence base and be able to use implementation lessons to inform further scale-up of the intervention to other districts and states, as well as to inform potential intervention scale-up in other settings.

Several challenges exist with using an SW-CRCT design, including a lack of consensus on the model of analysis [41]. Although the *Ottawa Statement* [43] and the Council for International Organizations of Medical Sciences (CIOMS) guidelines [44] provide relevant guidance to the design and conduct of Cluster Randomised Trials, neither document provides guidance specific to SW-CRCT. Other analytical challenges include modelling secular trends, time-varying intervention effect and modelling treatment effect heterogeneity. Different recruitment strategies may confound the statistical analysis. For intervention condition, the sample is drawn from cases identified by Champions. Champions are trained to identify people with CMD, there is a likelihood that they may identify people with higher GHQ scores, and this may confound the analysis and effect. We acknowledge this confounding effect due to different recruitment strategies, and the statistical analysis plan includes adjustment with baseline covariates to account for this confounding. Despite these limitations, we chose this design as being ethical and equitable, as all clusters receive intervention before the end of the trial. In addition, with a control and an intervention period in each cluster, outcomes can be compared within and across clusters which increase statistical power.

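### Recruitment route coincides exactly with treatment condition, so adjustment for baseline covariates cannot be shown to remove the confounding in the way the plan states

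*Protocol article*

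**What the plan says.** Under Recruitment, for controls, "a screening list is generated from the district electoral roll using a systematic random sampling method with pre-decided random start and random interval". For each group in each control period, "a screening list of 1800 participants is created and screened (GHQ-12 score of 3 and above) to achieve the target sample of 56 participants".

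The same section then says: "A different recruitment procedure is used in the intervention condition". A Champion identifies someone from an unstructured interview and intends to counsel them. The person agrees to their details being passed on, and the names are pooled across Champions. "The sample for the intervention condition is drawn from this master caseload list using a computer-generated random method". Data collectors then apply the same GHQ-12 cut-off of 3, before counselling starts. The stated reason for the separate route is to measure how accurately Champions identify cases.

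Under Data collection, "if the participant has a score of 3 or more, secondary outcome data is collected at the same time". Table 1 lists the SRQ, PHQ, GAD and WHO-DAS scales at baseline as well as the GHQ-12.

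Statistical analysis specifies a Hussey and Hughes mixed model with period and intervention fixed and cluster random, and adds: "The analysis will be adjusted for baseline covariates to account for potential imbalance arising due to different recruitment procedures". The Discussion concedes that Champions may pick people with higher GHQ scores and that this could confound the effect. It closes the matter with: "the statistical analysis plan includes adjustment with baseline covariates to account for this confounding".

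**The concern.** No control came through a Champion and no intervention participant came from the electoral roll. Even if the order of the steps is properly randomised, individuals enter the sample after the condition is known and by a route that the condition determines. Random sampling within each list does not change this, because the lists are different.

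Two people with the same baseline GHQ-12, one found by each route, need not have the same expected 3-month outcome without treatment. The person on the Champion's list may have a longer-standing problem, or may be at a passing peak of distress, or may be readier to seek help. The Discussion names only higher GHQ scores, which is the form of selection that baseline adjustment handles best. At stake is the primary contrast, which is meant to inform scale-up to other districts and states.

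**Working it through.** **1. The plan's own figure.** Inputs from Sample size and power calculations: 45% v 58% improved, ICC 0.1, 4 steps, 14 clusters per step, 4 participants per cluster per period, 80% power, alpha 0.05 (two-sided assumed). Five periods are inferred from one all-control period plus four steps: 4 groups × 5 periods × 56 = 1120, as stated.

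Hussey and Hughes variance with I = 56 clusters and T = 5 periods:
- U = 14(4+3+2+1) = 140; W = 0²+14²+28²+42²+56² = 5880; V = 14(16+9+4+1) = 420.
- Total variance 0.515 × 0.485 = 0.2498; τ² = 0.1 × 0.2498 = 0.02498; σ² = 0.9 × 0.2498 / 4 = 0.0562.
- Var = Iσ²(σ² + Tτ²) / [(IU − W)σ² + (U² + ITU − TW − IV)τ²] = 0.5699 / (1960 × 0.0562 + 5880 × 0.02498) = 0.5699 / 257.0 = 0.002217.
- SE = 0.0471; power = Φ(0.13/0.0471 − 1.96) = 78.8%.

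The sample size is reproduced to within 2 points of the stated power and is not in dispute. The SE is used below.

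**2. Aliasing.** Of the 4 × 5 = 20 group-period cells, 4+3+2+1 = 10 are control (560 people, all electoral roll) and 10 are intervention (560 people, all Champion caseload). Let X mark intervention and R mark the Champion route. The planned model plus a route effect is: outcome = period + cluster + θX + δR. Since R = X in every cell, the data identify only θ + δ. Cluster and period terms do not help.

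**3. What covariates would have to do.** Adjustment recovers θ only if, given the covariates, untreated recovery is the same by both routes. Nothing in the data can test this, because no untreated Champion-route sample exists.

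**4. What a residual bias b would do.** With a true effect of zero, P(significant) = Φ(b/SE − 1.96) + Φ(−b/SE − 1.96). With a true effect of 13 points and bias against the intervention, power = Φ((0.13 − b)/SE − 1.96).

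| b (points) | P(significant), no effect | Power, bias against |
|---|---|---|
| 0 | 5% | 79% |
| 2 | 7% | 65% |
| 5 | 19% | 40% |
| 10 | 56% | 9% |
| 13 | 79% | 2.5% |

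For scale, an unmeasured yes/no factor that shifts recovery by 30 points and is 30 points commoner in one route (both assumed) gives b = 0.30 × 0.30 = 9 points.

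**5. Can b be that large after adjustment?** This was simulated with no intervention effect. The result is the difference in recovery (GHQ-12 below 3 at retest), intervention minus control. Set A assumes about 6% screen positive, reliability 0.7–0.9 and Champion noise of 1–3 SD. Set B assumes 4% and 8% screen positive and a stable share of 0.5–0.85.

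| Champion selects on | A: GHQ-12 only | B: GHQ-12 only | B: plus SRQ-20, PHQ-9, GAD-7 |
|---|---|---|---|
| Current severity | −2 to −5 | −2 to −9 | −0.5 to −2 |
| Chronic severity | −5 to −13 | −9 to −17 | −6 to −14 |
| Transient peak | +8 to +17 | +6 to +17 | +7 to +20 |

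These figures show that the bias can take either sign and can survive adjustment. They do not estimate it. Every selection mechanism is assumed. Simulated control recovery (49–66% in A, 57–84% in B) exceeds the planned 45%. In a further variant, letting the Champion list reach the top 25% instead of the top 4–8% cut the chronic case from −8 to −19 down to −3 to −7.

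**The case against.** The strongest reply has three parts. First, the article explains why the routes differ and openly lists the confounding as a limitation. Second, it says covariates in the plural, and several severity scales are available. If Champions judge on described symptoms, current severity is the likeliest mechanism, and there the fuller adjustment leaves little. Third, naming covariates or fixing a bias analysis is ordinary analysis-plan content, and that plan is not shown.

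Much of this stands. Nothing is concealed, and an unnamed covariate list is not a finding. What does not stand is the assurance itself. Both sections say that adjustment deals with the confounding, and no covariate list can establish that when route equals condition. Disclosure that ends in that assurance does not cure it.

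Four stronger readings are tempting and are not supported:
- A reader might infer that the bias has a known direction or amount, or that any result is an artefact. The documents give no data on untreated prognosis by route.
- A reader might infer that only controls are selected on their baseline GHQ-12. The same cut-off is applied in both conditions at the baseline contact, so both groups regress towards the mean; only the difference matters, and it is unknown.
- A reader might infer a separate breach of intention to treat. Participants are recruited before counselling, are analysed by their cluster's assigned condition, and may have any number of sessions. The charge only restates the recruitment problem.
- A reader might infer that more covariates cure the problem. They help with selection on current severity. In set B they slightly enlarged the transient-peak bias, since the extra scales are taken at the same sitting as the GHQ-12.

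**Conclusion.** The concern holds in this form: recruitment route and treatment condition are fully aliased, so the statements in Statistical analysis and Discussion that baseline adjustment takes care of the confounding are wrong as written. Followed literally, the plan would present a comparison of differently recruited samples as an adjusted intention-to-treat effect.

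The sign and size of the residual bias cannot be determined from the documents. Under assumed mechanisms it ranges from near zero to about the 13-point target or more, in either direction. The sensitivity of the result to a given bias is firmer. It rests only on the protocol's design inputs, five inferred periods, a two-sided test and a normal approximation: the smallest significant difference is 1.96 × 4.71 = 9.2 points, so a bias of a few points matters.

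**What to change.** 1. **Wording.** In Statistical analysis and Discussion, replace the claim that adjustment accounts for the confounding. Suggested text: *Adjustment for baseline covariates only partly reduces confounding by recruitment route. The contrast compares samples recruited differently by condition and is not protected by randomisation at participant level.*
2. **Primary model.** Adjust for baseline GHQ-12 together with SRQ-20, PHQ-9, GAD-7 and WHO-DAS-12, all already collected at baseline. Describe this as a partial remedy for selection on current severity only.
3. **Tipping-point analysis.** Prespecify it before outcomes are examined by condition. For each assumed difference δ in untreated 3-month recovery between routes, subtract δ from the estimated risk difference and its interval. Use a range in both directions at least as wide as the 13-point target, for example −20 to +20 points, stated as an assumption. Report the δ at which the conclusion changes. As an illustration, an observed difference of exactly 13 points with SE 4.71 has an interval of 13 ± 9.2, or 3.8 to 22.2. A δ of +3.8 would remove significance and a δ of +13 would remove the effect. The model's odds ratio must first be converted to a risk difference.
4. **Conclusion.** Limit it to what survives that range.

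The cost is some wording, a few model terms and a more guarded conclusion; no new data are needed. Sampling the electoral roll in both conditions would have been the design remedy, but recruitment closed in August 2019. It would also have estimated a diluted effect: at an assumed 50% coverage, 13 × 0.5 = 6.5 points, with power Φ(0.065/0.0471 − 1.96) ≈ 28%.

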### Economic evaluation analysis

All data will be analysed in Microsoft excel. The ratio of costs and benefits will be calculated and will be presented as an ROI. This will inform whether *Atmiyata* intervention is a sound investment. Apart from this, the study will also provide information on the economic burden of CMD in the Mehsana district, which is of value to funders, policymakers and can be used for advocacy purposes. The economic burden of CMD will include direct medical cost (out of pocket expenses on drugs, diagnostics, consultations fees during outpatient visits and hospitalization), direct non-medical cost (out of pocket expenses on transport, food, accommodation while seeking treatment) and indirect cost (time spent by a patient and accompanied persons). As one of the secondary outcomes of the study is to understand the changes in the quality of life of the CMD patient using the EQ-5D, we will conduct a cost-utility analysis as an additional analysis in the economic evaluation. Cost-utility analysis expresses the value for money in terms of a multi-dimensional health outcome. The incremental cost-effectiveness ratio, in this case, is usually expressed as the incremental cost to gain an extra quality-adjusted life-year (QALY) [29]. Consolidated Health Economic Evaluation Reporting Standards (CHEERS) checklist will be followed while reporting the results of ROI and cost-utility analysis [42].

## Discussion

*Atmiyata* is a community-led intervention focused on reducing distress, particularly depression and anxiety symptoms in rural communities in India. The evaluation of the intervention through SW-CRCT, offers several unique opportunities. There is limited literature on SW-CRCTs conducted in low and middle-income countries, particularly involving mental health interventions. This study will contribute to this sparse evidence base and be able to use implementation lessons to inform further scale-up of the intervention to other districts and states, as well as to inform potential intervention scale-up in other settings.

Several challenges exist with using an SW-CRCT design, including a lack of consensus on the model of analysis [41]. Although the *Ottawa Statement* [43] and the Council for International Organizations of Medical Sciences (CIOMS) guidelines [44] provide relevant guidance to the design and conduct of Cluster Randomised Trials, neither document provides guidance specific to SW-CRCT. Other analytical challenges include modelling secular trends, time-varying intervention effect and modelling treatment effect heterogeneity. Different recruitment strategies may confound the statistical analysis. For intervention condition, the sample is drawn from cases identified by Champions. Champions are trained to identify people with CMD, there is a likelihood that they may identify people with higher GHQ scores, and this may confound the analysis and effect. We acknowledge this confounding effect due to different recruitment strategies, and the statistical analysis plan includes adjustment with baseline covariates to account for this confounding. Despite these limitations, we chose this design as being ethical and equitable, as all clusters receive intervention before the end of the trial. In addition, with a control and an intervention period in each cluster, outcomes can be compared within and across clusters which increase statistical power.

Another challenge is the lack of consensus on the cut-off score for depression using GHQ-12. Patel et al. [45] recommended a cutoff score of 7/8 for clinic-based populations. Goldberg et al. [46] suggested the best threshold for GHQ-12 scores varied from 1/2 to 6/7, with the most common cut-off score being 2/3. A recent Indian study confirmed an optimal cut-off score of 2 for community studies based on a receiver operating characteristic curve (ROC) analysis [47]. Taking all the above into account, we conservatively chose 3 as the cutoff score for our community study as it ensures the inclusion of community participants with mild to moderate CMD.

We anticipate challenges during data collection of the trial in a large community setting. Due to stigma and silence around mental ill health, there is a likely reluctance to participate in community mental health studies. Refusal to participate may also be due to the caste, gender, religion, and other social attributes. To address these challenges, data collectors are trained and re-trained on how to build rapport with participants and to maintain privacy and confidentiality. We recruited data collectors with diverse social attributes to represent Mehsana’s heterogeneous population.

Community members often change residence, or the address is incorrectly entered in the electoral register, which increases the time for identification of control condition participants. Data collection timelines also have to accommodate for community events such as farming season, religious festivities. Safety of data collection staff is an equally important concern given the large geographical area being covered. The team will conduct regular meetings to troubleshoot challenges on the field to adhere to the protocol.

Another challenge is to assess the extent to which Champions adhere to the counselling model that they have been trained in. A qualitative method is employed in to assess the fidelity. To do this, we will analyze audio recordings of counselling sessions, assessing a random sample of recordings amounting to 5% of the total counselling sessions delivered by Champions and the results of which will be published separately.

